##### Demographics

A brief section in the baseline questionnaire is used to assess characteristics, including age, gender, marital status, ethnicity, level of education, health background, employment information, sleep, smoking, alcohol, and eating behavior. Child-related demographic information is also collected, including the number of children, age of children, and gender of children. Importantly, items related to childcare are measured at all time points in order to assess whether participants have a formal or informal childcare provider, average hours of childcare daily, and difficulty finding childcare. Any changes in health are also assessed at all measurement points. Last, a commute section asks the total length of time (one way) it takes to get to the allocated choice activity, as well as the mode of transportation used to travel there.

##### Study evaluation

A brief end-of-program interview is conducted with two main aims: to gain a deeper understanding of parents’ attitudes and beliefs surrounding the importance of personal time or sport and to seek richer and in-depth information regarding their experiences with the program. Providing an opportunity to expand information verbally serves these aims and allows the program outcomes to be better explained. This is accomplished through conducting a 10-minute audio-recorded interview with a member of the research team. The interview questions touch on benefits, types of activities, changes in well-being, enjoyment, and barriers or the potential removal of barriers. Participants are then invited to provide any additional thoughts or suggestions on how the program might be improved. Last, the interviewer asks participants whether they will continue with their allocated condition after the study.

### Data management and confidentiality

Confidentiality procedures are outlined in the consent form (*see* Additional file 2) and explained during informed consent procedures conducted by the research assistant at the baseline assessment. In short, each participant is provided with an identification number. Hard copies of any documentation are kept in a locked and secure environment (locked laboratory and cabinets) at the University of Victoria. Any data or personal information stored on computers is kept on a secure server. Questionnaire data are stored on SurveyMonkey servers in Canada.

### Analysis strategy

Missing data will be inspected to determine the appropriate imputation procedures [43], and normality of all variables will be checked to determine whether any transformations are required. To determine whether psychosocial outcomes change over time similarly for all three conditions (i.e., to address objective 1), a level 1 model will be specified wherein the intercept (i.e., value of the outcome at baseline) will be allowed to vary randomly (i.e., vary across participants) and the slope for the linear trend will be constrained to be fixed (i.e., the same across participants), controlling for any significant covariates at level 2. Additionally, dummy variables will be created for condition (team sports: 1 = yes or 2 = no; individual sport: 1 = yes or 2 = no; control: 1 = yes or 2 = no) at level 2, with the team sport and individual sport variables being added to the model to predict the intercept and slope at level 1. In doing so, the control group is compared with the other two groups to determine if baseline psychosocial outcomes are similar across conditions and whether the change is similar across conditions. Follow-up analyses will be conducted for the group comparison. To determine whether participation within the team and individual sport conditions is explained by the Sport Commitment Model constructs (i.e., secondary objective 1), a time-varying covariate analysis will be used. For example, within the team sport condition, participation will be predicted by a level 1 model that includes a random intercept, fixed slope, and the time-varying Sport Commitment Model constructs. The same will then be done for the individual sport condition. To determine whether the change in the underlying motives explains the potential change in sport participation during the intervention similarly for all three groups (i.e., to address secondary objective 2), a time-varying covariate mediation analysis approach will be used following the procedure outlined by Krull and MacKinnon [44] for level 1 mediation. Briefly, the analyses needed to establish mediation will treat the underlying motives as time-varying covariates at level 1 of the model. Then, the dummy-coded condition variables will be entered at level 2 to determine if the mediation relationships are similar across groups. Finally, to determine whether there is a seasonal, gender, or sport type (within team or individual) difference across the primary and secondary outcomes (i.e., to address secondary objective 3), each variable will be entered into the various models at level 2 to predict the intercepts and slopes at level 1. Doing so will determine if they impact the change in the various outcomes across time.

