### Present research aims and hypotheses

The primary research question is whether a team sport condition increases positive psychosocial outcomes (quality of life, relationship satisfaction, social functioning, perceived parental stress, enjoyment) compared with an individual sport condition and a “personal time” control condition involving a choice-based pastime spent away from children. We hypothesize that the team sport condition will result in significantly greater changes in psychosocial outcomes than the other two conditions at the primary endpoint (3 months). Furthermore, the individual sport condition will also yield significantly larger changes in psychosocial outcomes than the personal time condition after 3 months of participation. Three additional secondary research questions will also be examined:

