### Outcome measures

#### Primary outcome measures

##### Change from baseline to 3 months in parental psychosocial outcomes

Assessments of psychosocial outcomes in all three groups are collected through online questionnaires (available on SurveyMonkey) and occur at three time points: baseline, 6 weeks, and 3 months.

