
### Justification of sample size

Given the hierarchical nature of the data (i.e., the three measurement occasions at level 1 were considered to be nested within the participant at level 2), the optimal design program for power estimation of hierarchical linear models [45] was used. With three measurement occasions, three groups, and a small to moderate effect size (0.40), a total of 207 participants (i.e., 67 parents per condition) were needed to show significant differences over time. Inclusive of a potential 25% attrition rate, the total sample size required is 240.

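### The primary model allows no between-participant variation in the time slope while testing condition differences in that slope, so its standard error is too small if participants within a condition change at different rates

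*Protocol article*

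**What the plan says.** All references are to the protocol article. The Analysis strategy section introduces the primary model with "To determine whether psychosocial outcomes change over time similarly for all three conditions (i.e., to address objective 1"). The intercept "will be allowed to vary randomly (i.e., vary across participants"), whereas "the slope for the linear trend will be constrained to be fixed (i.e., the same across participants"). Condition enters at level 2, with "the team sport and individual sport variables being added to the model to predict the intercept and slope at level 1".

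Read together, these sentences let the slope differ between conditions but leave no slope variation among participants within a condition. The outcome-measures section says that assessments "occur at three time points: baseline, 6 weeks, and 3 months". The hypothesis, under Present research aims and hypotheses, is that team sport gives "significantly greater changes in psychosocial outcomes than the other two conditions at the primary endpoint (3 months").

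The Analysis strategy section mentions no random slope, no residual covariance other than the default, no robust standard errors and no step to test whether slope variance is needed.

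**The concern.** The term that answers the primary question is a difference in slopes between conditions. Its sampling error has two parts: visit-to-visit noise, and real differences between people in how fast they change. The stated model sets the second part to zero. Any such variation is absorbed into the residual, where it is averaged over directions that do not bear on the slope, so only part of it reaches the standard error of the slope contrast.

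The protocol itself makes unequal change plausible. It asks, as exploratory questions, whether season, gender, family structure, child's age and sport type alter outcomes. It lets participants choose their own activity, and it grades attendance from none to complete. The moderator models for season, gender and sport type are separate analyses and do not repair the primary standard error.

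At stake are false-positive findings on the primary question and intervals that are too narrow, for the SF-12 and for the other psychosocial scales if they go through the same model.

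**Working it through.** **Inputs from the protocol.** Three visits (baseline, 6 weeks, 3 months); random intercept; fixed slope; condition × time tested.

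**Assumptions.** The protocol gives no correlations, slope variance or significance level. I assume a nominal two-sided 5%, equal variances at the three visits, complete data, model-based standard errors, independent level-1 residuals, and 3 months taken as 13 weeks. The protocol has no figure of its own to reproduce on this point.

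**Formula.** Let d be the centred visit times, SS = d′d, S the true 3 × 3 correlation matrix, and Q = I − J/3.
- True variance of a person's slope: d′Sd / SS².
- Variance assumed by the random-intercept model: [tr(QS)/2] / SS.
- Ratio R = true / assumed. Model SE / true SE = 1/√R. Actual error = 2[1 − Φ(1.96/√R)].

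**Worked case, adjacent 0.6, end-to-end 0.5.**
- Times 0, 6, 13 give d = (−6.33, −0.33, 6.67) and SS = 84.67.
- d′Sd/SS = 0.4997.
- tr(QS)/2 = 1 − (0.6 + 0.6 + 0.5)/3 = 0.4333.
- R = 0.4997/0.4333 = 1.153, so the SE ratio is 0.93.
- 1.96/√1.153 = 1.825, which gives an error of 6.8%.

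**Range of assumed correlations.**

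| Adjacent / end-to-end | R | SE too small by | Actual error |
|---|---|---|---|
| 0.60 / 0.60 | 1.00 | 0% | 5.0% |
| 0.60 / 0.55 | 1.08 | 4% | 5.9% |
| 0.60 / 0.50 | 1.153 | 7% | 6.8% |
| 0.70 / 0.60 | 1.199 | 9% | 7.3% |
| 0.70 / 0.49 | 1.377 | 15% | 9.5% |

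Equal spacing of the visits changes these figures hardly at all.

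**Same result in terms of slope variance.** With equally spaced visits, residual variance s² and slope variance τ², let L = τ²·SS/s². The true variance is proportional to 1 + L and the model's to 1 + L/2. Actual error is 5.0% at L = 0, 6.3% at 0.25, 7.4% at 0.5, 9.0% at 1, 11.0% at 2 and 12.9% at 4. As L grows without bound, R tends to 2, the SE is 29% too small and the error is 16.6%.

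**Simulation check.** At 60 per arm (240 × 0.75 / 3) with 20,000 replicates, the fixed-slope test rejected in 5.1%, 6.3%, 7.5%, 8.6%, 11.2% and 13.0% of replicates for L = 0, 0.25, 0.5, 1, 2 and 4. Estimating slope variance between people gave 4.8% to 5.3% throughout. Fitting the random-intercept mixed model itself at L = 1 (200 replicates) gave a mean model SE of 0.158 against an empirical SD of 0.192.

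**The case against.** The strongest reply is that the harm rests on quantities the protocol does not give. This stands. With equal correlations there is no inflation, and with mild decay the excess is about one percentage point. Unequal correlations need not inflate the error at all: 0.50 (baseline to 6 weeks), 0.55 (baseline to 3 months) and 0.60 (6 weeks to 3 months) give 4.9%. A reader might infer that type I error exceeds 5% for the primary outcome and every secondary scale. The protocol does not support that. Nor is 16.6% a forecast: it requires all within-person variation to be individual straight lines with no measurement error, which self-report questionnaires cannot meet.

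It can also be said that an article may leave residual structure and standard-error method to a fuller plan. That is fair for those two details, and robust standard errors would repair the problem. The constraint on the slope, however, is stated and not omitted, and a plan that follows the text inherits it.

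A reader might further object that a straight line is the wrong target when the endpoint is 3 months. That is not a separate error here. With complete data the fitted slope times 13 weeks weights the visits 13·d/SS = (−0.97, −0.05, +1.02), which is nearly the baseline to 3-month change. Linearity matters more only for participants with 6-week but no 3-month data.

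**Conclusion.** The point holds in conditional form and should be fixed. The stated model omits between-participant slope variance from the standard error of the very term it tests. If participants within a condition change at different rates, or correlation falls off between baseline and 3 months, the test is too liberal. Under the assumed correlations the actual error lies between 5.0% and 9.5%, with the moderate cases at 6.8% to 7.3%. With complete data the point estimate is essentially unaffected. The size rests on the assumed correlations, model-based standard errors and independent residuals. The mechanism and the direction under slope variation do not depend on the particular values chosen.

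**What to change.** Either of two changes to the Analysis strategy wording is enough:

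1. Keep the growth model and add a random slope, with its covariance with the intercept. This adds two covariance parameters and is estimable with three visits.
2. Use an unstructured 3 × 3 covariance: six covariance parameters instead of two. If preferred, also treat visit as a category and take the 3-month condition contrast as primary. This adds one visit effect and two condition × visit effects.

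Apply the choice to the primary outcome and to every other outcome analysed with this model, and state the standard-error method. Where slopes do not vary, almost nothing is lost; where they do, the intervals widen to their correct width. The Trial status section describes the study as ongoing, with analysis continuing through 2022, so on the document's own timetable the wording can be changed before the final analysis.

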Can participation in the team sports and individual sports conditions be explained by the constructs of the Sport Commitment Model?We hypothesize that participation will be predicted by sports commitment as per the tenets of the Sport Commitment Model. Commitment will be predicted primarily by enjoyment (+), social constraints from family obligations/involvement alternatives (−), and social involvement opportunities/personal investments (+).Can group differences among these motivational and behavioral outcomes be explained through a mediation model?We propose that the covariance of the assigned conditions on psychosocial outcomes will be explained by sport participation. In turn, the covariance between participation and assigned conditions will be explained by salient underlying motives from the Sport Commitment Model. In particular, enjoyment will explain the differences between both sport conditions, but the better psychosocial outcomes from team sports will be explained by the additional involvement opportunities of friendship and social interaction.Is there a seasonal, gender, dual/single parent, age of child, or type of sport difference across primary outcomes by assigned condition?Differences in season, gender, age of child, and type of sport are exploratory research questions. It is possible that both sport conditions may have participation lowered by weather conditions in the winter. Men may participate in sport more due to lower childrearing expectations; however, there is currently limited research to support this conjecture. Similarly, younger children may impact sport participation because of the considerable care needs of young children. Finally, it is possible types of sport could differ in their psychosocial outcomes for reasons such as the structure or environment of participation.

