### Randomization, allocation, and blinding

Randomization is performed by the project coordinator using Excel Sheet Randomization at a 1:1:1 allocation ratio. A research assistant then prepackages envelopes containing certificates that indicate condition assignment along with a list of potential ideas and resources for that condition. A second research assistant who is blind to participants’ condition presents the participants with their randomized allocation.

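### The condition-by-time model has no random slope: if change varies between parents within a condition, its slope standard errors are too small and type I error exceeds 5%

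*Protocol article*

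**What the plan says.** All of this is in the Protocol article. The Analysis strategy introduces the model with its purpose: "To determine whether psychosocial outcomes change over time similarly for all three conditions (i.e., to address objective 1". The intercept "will be allowed to vary randomly (i.e., vary across participants", while "the slope for the linear trend will be constrained to be fixed (i.e., the same across participants". The condition dummies are then used, with "the team sport and individual sport variables being added to the model to predict the intercept and slope at level 1". The common slope is therefore common within a condition, not across the whole trial, and the test of interest is whether slopes differ by condition.

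Under Outcome measures, the assessments "occur at three time points: baseline, 6 weeks, and 3 months". For the third secondary objective (season, gender and sport type), the Analysis strategy says "each variable will be entered into the various models at level 2 to predict the intercepts and slopes at level 1".

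The article gives no between-visit correlation, no slope variance and no significance level.

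**The concern.** A random intercept with independent, equal-variance residuals implies compound symmetry: the correlation between baseline and 3 months must equal that between baseline and 6 weeks. If parents in the same arm change at different rates, the two most distant visits correlate less. The model does not give this extra spread to the slope. It averages it over the linear and the curved parts of within-parent variation, so the variance reported for the slope contrast is too small.

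At stake are the width of the confidence intervals and the true level of the tests on the control-versus-sport slope contrasts, and of the slope-moderator tests built on the same structure.

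The article gives reasons to think slopes may vary within an arm. Parents choose their own activity in every arm (Intervention description). The attendance item runs from no adherence to no missed session (Sport commitment and sport participation). Season, gender and sport type are tested as predictors of slope.

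**Working it through.** The plan gives no figure to reproduce on this point, so the check is algebra with assumed inputs.

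**Inputs from the article.** Three visits, taken as equally spaced at times 0, 1, 2; "1:1:1 allocation ratio"; random intercept, no random slope; condition predicts the slope. A target of 240 gives 240 / 3 = 80 per arm for simulation, with the stated 25% attrition.

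**Assumed inputs.** A two-sided 5% test; independent, equal-variance level 1 residuals in the fitted model; the correlations and variance ratios below.

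**Step 1: correlation form, unit variance at each visit.** Write r12, r23 and r13 for the correlations between visits. The linear contrast is L = (Y3 − Y1)/√2 and the curved contrast is Q = (Y1 − 2Y2 + Y3)/√6.

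- Var(L) = 1 − r13
- Var(Q) = 1 − (2/3)(r12 + r23) + r13/3

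The precision of the slope depends on Var(L). The random-intercept model uses the mean of Var(L) and Var(Q) instead. With ratio R = Var(L) / mean, the actual type I error is 2·P(Z > 1.96/√R).

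| r12, r23, r13 | Var(L) | Var(Q) | Mean | R | Reported SE / true SE | Type I error |
|---|---|---|---|---|---|---|
| 0.70, 0.70, 0.70 | 0.300 | 0.300 | 0.300 | 1.00 | 1.00 | 5.0% |
| 0.70, 0.70, 0.60 | 0.400 | 0.267 | 0.333 | 1.20 | 0.91 | 7.4% |
| 0.70, 0.70, 0.50 | 0.500 | 0.233 | 0.367 | 1.36 | 0.86 | 9.3% |
| 0.75, 0.75, 0.55 | 0.450 | 0.183 | 0.317 | 1.42 | 0.84 | 10.0% |

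**Step 2: slope-variance form.** Let r be the between-parent slope variance (per six-week step) divided by the residual variance s². The true variance of one parent's slope is s²/2 + r·s². The model reports (s² + r·s²)/2. Hence R = (1 + 2r)/(1 + r).

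| r | R | Reported SE / true SE | Type I error, one contrast | Joint 2-df test |
|---|---|---|---|---|
| 0 | 1.00 | 1.00 | 5.0% | 5.0% |
| 0.1 | 1.09 | 0.96 | 6.1% | 6.4% |
| 0.25 | 1.20 | 0.91 | 7.4% | 8.2% |
| 0.5 | 1.33 | 0.87 | 9.0% | 10.6% |
| 1 | 1.50 | 0.82 | 11.0% | 13.6% |

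The two forms agree: R = 1.20 gives 7.4% in both.

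**Step 3: simulation, 80 per arm, 25% dropout, REML.**

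- Correlation form, 1,500 to 2,000 runs, r13 = 0.60 and 0.50 with adjacent correlations of 0.70: the planned model rejected 7.3% and 9.05%; an unstructured covariance rejected 5.6% and 5.05%.
- Slope-variance form, about 480 to 600 runs, one contrast under the planned model: 5.2% at r = 0, 6.8% at 0.25, 12.0% at 0.5 and 9.8% at 1. The Monte Carlo standard error is about 1 to 1.5 points, so these show that inflation is present but rank the scenarios poorly.
- With a random slope added at r = 0.5 (200 runs), one contrast rejected 7.0% and the joint test 5.0%. With Monte Carlo errors of about 1.8 and 1.5 points, both are compatible with 5%.

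**The case against.** **The inflation is not certain.** A reader might infer that the planned test necessarily exceeds 5%. The documents do not support that: with zero slope variance it is exactly 5%, and at r = 0.1 it is only 6.1%. The direction can even reverse. Correlations of 0.60 between adjacent visits and 0.70 between baseline and 3 months give Var(L) = 0.300 against a mean of 0.367, R = 0.82 and about 3% type I error. That pattern is less plausible, but the article does not exclude it. This objection stands, and the point is therefore conditional.

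**The article does not state the residual covariance or the standard-error method.** A serially correlated residual or robust errors would be compatible with the text and could be in an analysis plan that is not shown. That silence is not held against the plan. The slope constraint is a stated choice, however, and it is open to comment as written.

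**Testing a moderator is not expecting one.** The article calls these questions exploratory, and in the moderator models the named variables absorb the part of the slope variation they explain. This stands. The tests show that the authors allow for unequal change, not that they predict it. The remark that "younger children may impact sport participation because of the considerable care needs of young children" concerns participation, not the spread of outcome change, and is not relied on here.

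**Three stronger readings fail.**

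- The error does not favour sport. Standard errors that are too small raise two-sided rejection equally in both directions, including false results in favour of control.
- Slopes are not forced to be equal across arms, since condition predicts them.
- Not every primary comparison is shown to come from this model. Group comparisons are left to follow-up analyses of unstated form, and team versus individual sport may be tested there.

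**Conclusion.** The concern holds in conditional form. The plan tests condition-by-time with residual slope variance set to zero within each condition. If change varies between parents within a condition, or correlation falls with time, slope standard errors are too small and two-sided type I error exceeds 5%. Over the assumed range it is about 6% to 11% per contrast; with equal correlations there is no error. The result rests on the assumed correlations and variance ratios, a nominal two-sided 5% level, equally spaced visits, and independent, equal-variance residuals.

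The design does not force the constraint. Three visits give six variances and covariances, enough for the four parameters of a correlated random intercept and slope. This is a cheap improvement that should be made. The documents do not show that the primary test is invalid.

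**What to change.** In the Analysis strategy, replace the clause that fixes the slope across participants. State that the condition-by-time model will use an unstructured 3×3 within-parent covariance, or a correlated random intercept and random slope, fitted by REML. If it does not converge, keep the random intercept and use parent-clustered robust standard errors. Apply the same rule to the slope-moderator models.

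The cost is one sentence and two extra variance parameters for the random slope (four parameters instead of two), or four for the unstructured covariance (six instead of two). In the assumed scenarios with falling correlation, standard errors become about 10% to 19% larger (√1.20 = 1.095, √1.36 = 1.17, √1.42 = 1.19). That is the precision the data would actually support. If slopes do not vary, little is lost. The Trial status section has analysis continuing through 2022, so on the article's own timeline the change can be made before the final analysis.

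### Letting condition predict the baseline intercept makes the main contrast a difference in change scores: unbiased, but less precise than a baseline-adjusted comparison

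*Protocol article*

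**What the plan says.** The Analysis strategy section of the protocol article describes a two-level growth model. At level 1, "the intercept (i.e., value of the outcome at baseline) will be allowed to vary randomly", and the linear slope is fixed, without a random component. Condition enters at level 2, with "the team sport and individual sport variables being added to the model to predict the intercept and slope at level 1". The section says what this achieves: "the control group is compared with the other two groups to determine if baseline psychosocial outcomes are similar across conditions", and likewise for change. Other covariates come in by "controlling for any significant covariates at level 2"; none is named and no criterion is given.

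The assessments "occur at three time points: baseline, 6 weeks, and 3 months", and the primary outcome heading is "Change from baseline to 3 months in parental psychosocial outcomes". The section on intervention description, schedule and procedures puts the baseline questionnaire first and randomisation after it.

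**The concern.** Because baseline is measured before randomisation, the arms have the same expected baseline score. A model that estimates a separate baseline mean for each arm ignores this, and testing whether those means are similar tests a hypothesis already known to be true. The practical cost is precision: a chance imbalance at baseline is subtracted in full from the 3-month difference, not in proportion to how well baseline predicts the 3-month score. The loss applies to every arm comparison on every psychosocial outcome analysed this way.

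**Working it through.** **Inputs from the protocol article.** Three occasions (0, 6 weeks, 3 months), taken as equally spaced; random intercept, fixed linear slope, condition on both (Analysis strategy); effect size 0.40, 67 per condition, 240 enrolled, 25% attrition (Justification of sample size).

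**Assumptions, because the article does not give them.** Correlation r between baseline and 3 months, ranged from 0.3 to 0.8; 0.40 read as raw-score SD units; two-sided alpha 0.05.

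**The plan's own figure.** The article states no variance or power for this contrast. Its nearest figure is 67 per condition. For a change-score comparison with effect 0.40 SD, 80% power (also assumed) needs 67 per arm only if r is about 0.66; at r=0.5 it needs 99. After 25% attrition, 240 × 0.75 = 180, or 60 per arm, which is the number used below.

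**Step 1: what the planned contrast is.** With complete data at times 0, 1, 2, a random-intercept model estimates each arm's slope from the weights (−1, 0, 1)/2. Twice the slope is therefore the mean of (3-month score − baseline), and the arm contrast in slopes, scaled to 3 months, is the difference in mean change. Generalised least squares confirms this. At r=0.5, with one participant per arm and SD 1, the variance of the contrast is 2.000 under both the planned model and the change score. With visits at weeks 0, 6 and 13 it is 1.996, so slightly unequal spacing hardly matters. In one simulated data set (67 per arm), the fitted model and the raw change-score difference both gave 0.3641.

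**Step 2: variance per participant, SD 1.**
- Planned (change score): 2(1 − r)
- Baseline-adjusted: 1 − r²
- Ratio: (1 − r²) / [2(1 − r)] = (1 + r)/2

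A common baseline mean with visit as a categorical factor gives the same ratio.

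**Step 3: size.** Two-sample t-test power, 60 per arm, effect 0.40 SD:

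| r | 2(1−r) | 1−r² | Ratio | Power, planned | Power, adjusted |
|---|---|---|---|---|---|
| 0.3 | 1.40 | 0.91 | 0.65 | 45% | 62% |
| 0.5 | 1.00 | 0.75 | 0.75 | 58% | 71% |
| 0.6 | 0.80 | 0.64 | 0.80 | 68% | 78% |
| 0.7 | 0.60 | 0.51 | 0.85 | 80% | 86% |
| 0.8 | 0.40 | 0.36 | 0.90 | 93% | 95% |

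**Step 4: do the significant covariates repair this?** No. In the simulated data, adding a prognostic level 2 covariate to the intercept left the contrast at 0.3641 with standard error 0.182. A covariate that is constant over time cancels out of a within-person change.

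**The case against.** The planned model answers the stated question. The primary outcome is change from baseline to 3 months, and a growth model with condition on intercept and slope estimates it without bias under randomisation. This stands. A reader might infer that the plan gives a wrong or biased treatment effect, or that baseline data are thrown away; neither is so. Baseline is used, but with a fixed weight of 1 and not its regression weight.

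The baseline comparison is a by-product of the fitted model, and the text attaches no decision to it. This also stands: the comparison is uninformative, not harmful in itself.

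It is tempting to blame the covariate rule for the change-score form, or to say that picking significant covariates puts the primary p-value at the mercy of model selection. The documents do not support either. The free intercept alone produces the change-score form. With complete data, a covariate on the intercept leaves the contrast unchanged; in a simulation with 25% dropout it moved the estimate by only about 0.01. Only the secondary analyses of season, gender and sport type let other variables predict the slope.

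The absolute powers are also open to challenge. The article does not say on what scale 0.40 is measured and states no alpha. A completers-only t-test ignores 6-week data from participants who drop out. In a simulation with 80 per arm and 25% dropout, the planned model had about 63% power at r=0.5 and about 83% at r=0.7, against 58% and 80% in the table. The variance ratio for complete data does not depend on the scale of the effect or on alpha.

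Finally, a reader might infer that the gain more than makes up for falling from 67 to 60 per arm. That does not hold throughout: at r=0.8, the adjusted analysis with 60 has 95.2% power and the planned analysis with 67 has 95.3%. The shortfall in numbers is a separate matter.

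**Conclusion.** The point holds as a matter of efficiency. The planned contrast is valid but discards the knowledge that the arms share one baseline mean. With complete, equally spaced data, the adjusted analysis has 0.65 to 0.90 of the planned variance for r from 0.3 to 0.8. The identity is exact under those conditions and approximate with dropout or unequal spacing. The gain is large if the scales are only moderately stable over 3 months and small at r=0.8, where power moves from 93% to 95%. The open-ended covariate rule is a minor matter of prespecification, with no demonstrated effect on the primary contrast.

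**What to change.** - Remove the condition terms from the intercept, so that all arms share one baseline mean and condition acts only on the post-baseline visits. Alternatively, analyse the 6-week and 3-month scores with the baseline score as a covariate.
- Drop the between-arm test of baseline similarity.
- As a minor accompanying change, name any further covariates in advance and keep them whatever their p-values.

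No new data are needed, since the baseline scores are already collected. The cost is rewording the analysis plan and documenting the change. The article's Research ethics processes section sends protocol changes to the ethics board and then to the registry. Because 109 participants had already completed the 3-month measures, the change should be dated and made before outcomes are compared by arm.
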